### **6.2.5. Self-Reported Physical Function/Disability and Physical Activity – Accelerometry**

**Self-Reported Physical Function/Disability** is assessed with a modified version of

disability instrument that was used in LIFE-P, now called the Pepper Assessment Tool for Disability (PAT-D). Based on factor analysis, 4 items were omitted from the original instrument (doing errands, preparing meals, feeding, and raising arms above head), leaving 19 items covering 3 domains: (1) basic ADLs (moving in and out of a chair, moving in and out of a bed, gripping with hands, using toilet, dressing, getting in and out of a car, and bathing); (2) mobility (walking several blocks, lifting heavy objects, walking 1 block, lifting/carrying 10 lbs, climbing several flights of stairs, and climbing 1 flight of stairs); and (3) instrumental ADLs (light housework, participating in community activities, managing money, visiting with relatives or friends, using the telephone, and taking care of a family member).

For each item, respondents answer whether they experience 1) no difficulty, 2) a little difficulty, 3) some difficulty, 4) a lot of difficulty, 5) unable to do or, 6) did not do for other reasons. Answers are averaged across the items, in order to better assess the overall perceived disability burden by a person.

As in LIFE-P, we will add two items to the disability instrument, giving a total of 21 items. These are “walking across a small room” and “walking a quarter of a mile.” These two items have been used previously as the single outcome of interest for studies on mobility disability. In addition, for the basic ADLs (including walk across a room, but not gripping with hands) we plan to ask whether the participant receives help from another person to complete the task. This will allow us to calculate a Katz ADL score. The disability questionnaire will be administered at the first screening visit, and at all subsequent visits. An abbreviated Disability Questionnaire will be administered at the 18, 30, and 42 month visits.

A proxy ADL questionnaire is administered when a participant is not available to complete a follow-up assessment or is deemed to be cognitively impaired based on the Six-item screener. The assistive device questionnaire inquiring about the use of a walker or cane is administered for all visits at which the 400 m walk test is not attempted.

**Self reported physical activity** is monitored by means of the Community Healthy Activities Model Program for Seniors (CHAMPS) Activities Questionnaire a validated questionnaire that takes about 15 min to complete. The questionnaire assesses the weekly frequency and duration of various physical activities typically undertaken by older adults. This instrument is administered at the first screening visit, and at the 6-, 12-, 24-, 36-month, close-out, and PIV assessment visits. In addition, for a subset of activities, the specific amount of time will be ascertained to supplement the categorical response. A slightly modified version that includes 18 items will be used (CHAMPS-18).

### **Accelerometry**

The ActiGraph GT3X (ActiGraph™ LLC, Pensacola, FL) is used to assess the relative impact of interventions on physical activity over time. The ActiGraph is a small (3.8 cm x 3.7 cm x 1.8 cm, 27g) triaxial accelerometer that is designed to detect accelerations in three axes. Output from the ActiGraph is in the form of step counts, body positions (standing and sitting/lying) and activity counts for a specific time period (i.e., epoch). Activity count cut-points (e.g., counts·min) can be identified to determine the amount of time a participant spends in sedentary, light, moderate, hard, or vigorous activity. Accelerometry will be measured for 7 consecutive days at baseline, 6, 12, 24-month, and the PIV visits, in all participants randomized at each site.

**Determination of activity count cut-points.** Individualized activity count cut-points for each participant will be determined during the 400-m walk. The average count·min generated by a participant during the 400-m walk will serve as his/her individualized activity cut-point and can be used to evaluate the 7-day accelerometry data. The ActiGraph will be initialized prior to the participant's assessment visit and

programmed to record data in one-second epochs.

The monitor is then attached to the participant's waistline using a belt and placed along the right mid-axillary line. Staff will record the start time and end time for the walk from the computer laptop used to initialize the monitor. The beginning and end of the 400-m walk will be identified on the ActiGraph through visual inspection and the time stamp corresponding to the time when the 400-m walk occurred. As a result, the activity counts associated with the 400-m walk can be easily identified during subsequent analyses.

**7-day accelerometry.** At the conclusion of the walk, participants will keep the monitor on and wear it for the 7 days immediately following their clinic visit. During the 7-day monitoring period, participants will be asked to put the monitor on each morning (after dressing) and remove the monitor just prior to going to bed at night. The monitor will also be removed for bathing, showering, or any other activity that might result in exposure to water. Participants will be instructed to contact research staff by telephone with any questions about monitor use. Following the 7th complete day of activity monitoring, participants will return their activity monitor to research staff via mail.

Accelerometry data from the 400-m walk and 7-day assessment will be downloaded from the monitor and securely transmitted to DMAQC for data cleaning and analysis.

#### **6.2.6. Process Measures**

A brief battery of tests is employed to evaluate psychological processes that are theoretically linked to adherence and success with the interventions. These include items related to performance efficacy, barriers efficacy, satisfaction with function and motivation for physical competence. This brief test battery is collected via self-administration on all participants at baseline, 12 months and 30 months. At baseline, a survey of each participant's local environment will also be obtained to examine the role of physical environmental barriers on physical activity participation and adherence.

#### **6.2.7. Vital Signs**

Prior to randomization and the 6, 18, 30 months, and PIV visits, data are collected on sitting blood pressure, heart rate, and weight. Body height is measured once prior to randomization. Waist circumference is measured at baseline and at the 24 months visit. The blood pressure assessments will allow the determination of the incidence of hypertension and serve as basis for a temporary exclusion. The other measures are collected primarily for descriptive purposes.

#### **6.2.8. Medication Inventory**

Many older adults use both prescription and non-prescription pharmaceutical products. The use of these products is of interest for several reasons. Their use is an important indicator of overall health, and the nature of the drugs taken is a strong indicator of clinically manifest disease. The response to the intervention may be enhanced or diminished by some drugs. Finally, individuals who use nutritional supplements, herbs or other complementary products may have a stronger sense of health self-efficacy, and thus the use of these products could be related to study adherence. All participants are asked to bring all prescription and non-prescription medications taken in the past two weeks to their first pre-randomization screening visit and subsequent annual follow-up visit. Medications include: pills, tablets, drops, salves, injections, creams/ointments, inhalers, suppositories and dermal patches. Non-prescription medications include: vitamins, aspirin, laxatives, dietary supplements, and herbal preparations. The name, strength and formulation of each product are transcribed. These medications are coded according to

formulation for use in subsequent data analyses. This method of drug assessment has been shown to be valid in older adults. The medication inventory is administered at baseline and at the 12 month clinic visit.

#### 6.2.9. ECG

A twelve lead ECG is performed at the initial visit for safety purposes. The ECG is reviewed by the study physician at each field center to assess potential exclusion criteria. In addition, to assess silent myocardial infarction, ECG will be performed at 18 months, and at closeout only if the measures were missed at 18-month follow-up visit or if the 18-month follow-up visit occurred more than one year prior to the closeout visit.

#### 6.2.10. Social, Economic and Health Related Questions

For descriptive purposes, the following participant characteristics are collected: age, gender, race, living situation, household composition, marital status, educational level, smoking status, alcohol consumed, employment status, occupation, volunteer work, income level and chronic conditions.

#### 6.2.11. Cognition

Cognitive function is assessed at baseline (both computer battery and non-computer based battery) and at 18 (computer battery only), 24-months (non-computer based battery only), and at the PIV (non-computer based battery only) visits in all participants. Participants who are unable to take the battery components at 18 or 24 months will be allowed to take them at the 30 month visit. The LIFE Study cognition assessment battery measures were selected because they have been used often in research examining aging and cognitive disorders and have been improved by either cognitive or physical activity interventions. As described in Section 3.3, the DSST and the HVLT are the two cognitive measures upon which the cognition outcome in LIFE is powered and will be assessed in the following manner:

1. **Digit Symbol Substitution Test (DSST)** is a measure of attention and perceptual speed in which participants are given a series of numbered symbols and then asked to draw the appropriate symbols below a list of random numbers. The score is the number of correctly made matches in 2 minutes (120 seconds).
2. **The Hopkins Verbal Learning Test (HVLT)** is a 12-item list learning and memory test designed for brief, easy administration with proven participant tolerability in a variety of populations. The HVLT requires the participant to listen to a list of 12 words and repeat as many as possible. The task is repeated twice, for a total of three trials. Approximately 20 minutes later, s/he is asked to recall as many words as possible. The participant is also presented a yes/no delayed recognition trial consisting of a randomized list that includes the 12 target words and 12 non-target words, six of which are drawn from the same semantic categories as the targets. Scores for immediate recall (total of three trials), delayed recall, and recognition are calculated into a summary score.

In addition:

3. **The Modified Mini-Mental Status Exam (3MSE)** will be administered as a test of global cognitive function which assess a broad variety of cognitive measures. This is an expanded 100 point version of the original Folstein MMSE and has been used in large epidemiological studies and clinical trials to effectively screen for persons experiencing impaired cognition and estimate incident Mild Cognitive Impairment (MCI) or dementia (see below).

4. **The Modified Rey-Osterrieth Complex Figure (Rey-O)** copy and immediate recall will be administered as a measure of visuospatial skills. The Rey-O has published normative data and there are standard qualitative scoring schemes that provide important information about the nature of underlying cognitive impairment.

The final components of the cognitive battery will be a computer-based battery of tests focused on elements of executive function:

5. **Eriksen flanker task** measures response inhibition. Participants are presented with an arrow facing either right or left and are asked to press a key indicating its direction. The target displays can be neutral (no flankers), congruent (flanker arrows point in the same direction as the target arrow), or incongruent (the flanker arrows point in the opposite direction).
6. **N-Back Test** measures working memory. Participants see individual letters at a 2-second rate on a computer screen and are asked to indicate whether the presented letter is the same as the nth back letter, with n equal to 1 and 2.
7. **Task Switching** measures attentional flexibility. Participants are asked to quickly alternate between performing two different tasks, which requires executive function to reconfigure the cognitive system each time the task demands shift. They will be shown single digit numbers and asked to determine if they are odd or even, which will alternate with presentation of single letters for which they will have to indicate whether the letter is a consonant or vowel.

Participants with known dementia or who score below education-based cutoffs on the 3MSE will be excluded from the LIFE trial during the screening visit (see 4.2.1). In order to classify cognitive status on all participants enrolled at baseline, those who score 76 - 88 (English speaking non-African American) or 70-88 (African American and Spanish speakers) on the 3MSE will need an assessment of daily functioning with regard to cognitively demanding tasks. Thus, we will administer the **Functional Activities Questionnaire (FAQ)** to a proxy (family member, close friend or caregiver). The FAQ is a brief, 10 item questionnaire, that has been validated for the purposes of ascertaining the impact of cognition on important daily functions. Results from the FAQ in combination with the cognitive tests will be used to classify the cognitive status of all participants at baseline.

All tests listed above will be re-administered at follow-up. At the 18 month visit the computer-based battery will be administered. At the 24 month and PIV visits, in addition to 3MSE, HVLIT, DSST, and Modified Rey-O, these additional assessments will be administered to all participants: Category Fluency – Animals, Boston Naming Test (15 item), Trails A & B (See Appendix A). For participants not able to complete any aspect of the cognitive test battery at their 18 or 24 month visit, it will be administered at their 30 month visit. If an in-person assessment is not possible, a Telephone Interview for Cognition (TICS) will be obtained. If no contact with the participant is possible (severe cognitive impairment, death), a Dementia Questionnaire (DQ) will be administered to a proxy.

#### 6.2.12. Health-Related Quality Of Life

The following key components of HRQL are assessed at baseline, year one and year two via self-administration:

1. Depressive symptoms are assessed with the 11-item version of the Center for Epidemiologic Studies Depression Scale (CES-D), which queries about depressive

symptoms experienced in the previous week. Scores are transformed using the procedure recommended by Kohout et al. to make it compatible with the full 20-item instrument. Total scores range from 0 to 60, with higher scores indicating more depressive symptoms.

2. Energy and fatigue level is assessed by the 6 fatigue and energy items from the Modified Exercise-induced Feeling Inventory. Each item is rated on a 6-point scale, which focuses on the amount of time that individuals experienced fatigue or energy related feelings during the past week.
3. Perceived stress is assessed by the 10-item version of the Perceived Stress Scale (PSS), which assesses perceived global stress on a 5-point Likert scale. The items were designed to tap how unpredictable, uncontrollable, and overloaded respondents find their lives.

#### **6.2.13. Quality of Well-Being Scale (QWB-SA)**

The self-administered version of the Quality of Well-Being Scale (QWB-SA) is used to assess general quality of life and for the subsequent cost-utility analyses.

Participants are asked to complete the questionnaire (described below) at home prior to the second screening visit and all subsequent visits. These forms are reviewed for completeness during the relevant screening/clinic visit. The QWB is a comprehensive measure of health-related quality of life that assesses health symptoms and functioning. The observed level of function and the subjective symptomatic complaints are then weighted by preference, or utility, on a scale that ranges from 0 (dead) to 1.0 (optimum function). The weights were obtained from independent samples of judges who rated the desirability of observable health states. Several studies have shown that the weights do not vary as a function of demographic variables, including race, income, and gender.

The QWB-SA takes about 10 minutes to complete. The assessment covers an extensive list of symptoms including both acute and chronic conditions and psychological well-being is well represented. The questionnaire asks about symptoms and functioning over the previous 3 days, minimizing recall bias, and providing a "point in time" expression of health. The measure has been selected for several multisite NIH clinical trials, including the National Emphysema Treatment Trial (NETT), the Diabetes Prevention Program (DPP), and portions of the Prostate, Lung, Colorectal, and Ovarian screening trial (PLCO). In addition, the QWB has been used in a variety of clinical studies for a range of medical and surgical conditions that include COPD, AIDS, cystic fibrosis, diabetes mellitus, atrial fibrillation, lung transplantation, arthritis, cancer, schizophrenia, and many other conditions.

#### **6.2.14. Health Care Utilization**

Health care utilization is assessed at the second screening visit and all subsequent visits using a self-administered questionnaire developed at the University of California San Diego. The measure consists of 12 questions that ask about the frequency of various types of health care utilization over the previous 6 months. The questions ask about utilization of hospital days, emergency care, urgent care, primary care, telephone calls, prescriptions, and medical equipment. Health care costs are calculated by multiplying the frequency of each service by the prevailing community charge. The measure has been validated in a clinical trial of patients with chronic obstructive pulmonary disease.

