Level of ADL disability will be repeatedly measured as a continuous, score variable. A comparison of average post-randomization levels of ADL disability between intervention groups will be performed using mixed-effects analysis of covariance techniques appropriate for repeatedly measured outcomes. These models will contain variables representing field center, gender, a follow-up time effect, the baseline level of ADL disability and an intervention effect. Initially, we will explore the appropriateness of a model containing random intercepts and slopes (for follow-up time). The appropriateness of a model containing a fixed effect for the intervention by follow-up time interaction will be evaluated.

**Secondary aim #7** will be to assess the cost-effectiveness of the intervention.

Cost-effectiveness analyses will be conducted following the guidelines of the Panel of Cost-Effectiveness in Health and Medicine. The ratio of direct costs of the physical activity intervention to the amount of quality-adjusted life years (QALYs) produced is calculated. Health care costs will be estimated and differences between the physical activity and lifestyle intervention groups will be calculated to examine whether any cost-offset may occur. LIFE takes a societal perspective. The trial uses the health education intervention as the comparator for all cost-effectiveness analyses. Results will be described as the incremental cost-effectiveness over the comparator. Sensitivity analyses will be conducted to examine whether the cost-effectiveness results change as a function of any estimates or assumptions made in the process. Decision modeling will be used to estimate long-term cost-effectiveness beyond the 1-year time horizon for which data collection is planned. Future health care costs will be discounted at a rate of 3% for any calculations or projections beyond the first year of follow-up.

**Tertiary aim #1** will be to explore the effects of the interventions on MCI/D.

Logistic regression will be used to assess whether the proportion of participants who convert to the composite outcome of MCI/D from baseline varies by intervention assignment. Baseline level of global cognitive function (3MSE score) will be used as a covariate in these analyses.

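### Health care use is priced at community charges with no conversion to resource cost, although the analysis is societal, so any cost-offset is scaled by the mark-up

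*Protocol*

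**What the plan says.** Section 6.2.14 describes a 12-question self-report of service use over the previous 6 months, covering hospital days, emergency, urgent and primary care, telephone calls, prescriptions and equipment. It then sets the price: "Health care costs are calculated by multiplying the frequency of each service by the prevailing community charge". Section 10.6 repeats the rule in the same words.

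Section 12.2, secondary aim #7, sets the frame for the economic analysis:

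- Perspective: "LIFE takes a societal perspective".
- Ratio: "The ratio of direct costs of the physical activity intervention to the amount of quality-adjusted life years (QALYs) produced is calculated".
- Health care costs come in a separate sentence, where differences between the two "groups will be calculated to examine whether any cost-offset may occur".
- Reporting: "Results will be described as the incremental cost-effectiveness over the comparator".
- Robustness: "Sensitivity analyses will be conducted to examine whether the cost-effectiveness results change as a function of any estimates or assumptions made in the process".
- Standard: "Cost-effectiveness analyses will be conducted following the guidelines of the Panel of Cost-Effectiveness in Health and Medicine".

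The same paragraph plans decision modeling beyond the first year, with future health care costs discounted at 3%. No section names a unit-cost source other than the charge, or a conversion from charge to cost.

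**The concern.** A societal analysis should count what the care consumes. A charge, in the ordinary sense of the word, is what a provider bills, and it can sit well above the resource cost. The protocol calls the product of frequency and charge a cost and stops there. This is a rule stated twice, so it is more than a detail left open for later.

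Cost-effectiveness is a named secondary outcome. The question whether the physical activity program pays back part of its cost through lower health care use is answered by the very difference that the charge inflates. If use falls in the program arm, the saving looks too large. If use rises, the extra burden looks too large. Either could change what a health system concludes about adopting the program.

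**Working it through.** **Inputs.** Price rule: sections 6.2.14 and 10.6. Perspective, ratio and cost-offset: section 12.2, aim #7. The protocol gives no cost, charge, mark-up, QALY gain or cost per QALY, so there is no stated figure to reproduce. The ranges below are assumptions.

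**Step 1: the offset.** Let S be the between-arm saving in health care at resource cost, r the cost as a share of the charge, and k = 1/r. Priced at charges, the saving becomes k × S.

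- r = 0.60: k = 1/0.60 = 1.67
- r = 0.30: k = 1/0.30 = 3.33
- r = 1: k = 1, no error

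If S = 0, the result is zero whatever k is. If S is negative (more care in the program arm), the excess is magnified by the same factor.

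**Step 2: which ratio is touched.** Let C be the program cost and ΔQ the QALY gain.

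- As spelled out in section 12.2: C/ΔQ. Health care use does not appear, so k has no effect.
- With the offset netted in: (C − kS)/ΔQ in place of (C − S)/ΔQ. With f = S/C, the relative error is (1 − kf)/(1 − f) − 1.

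| f (assumed) | k = 1.67 | k = 3.33 |
|---|---|---|
| −0.2 | 1.333/1.2 − 1 = +11% | 1.667/1.2 − 1 = +39% |
| 0 | 0% | 0% |
| 0.1 | 0.833/0.9 − 1 = −7% | 0.667/0.9 − 1 = −26% |
| 0.2 | 0.667/0.8 − 1 = −17% | 0.333/0.8 − 1 = −58% |
| 0.4 | 0.333/0.6 − 1 = −44% | −0.333/0.6 − 1 = −156% |

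In the last cell the net cost turns negative: a program that recovers 40% of its cost would be reported as cost-saving. This happens whenever kf exceeds 1, that is f above 0.30 at k = 3.33 or above 0.60 at k = 1.67.

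**Step 3: unequal mark-ups.** A single multiplier k assumes the same mark-up for every service. If mark-ups differ, charges also change the relative weights. Illustration with assumed figures: the program saves USD 1,000 of inpatient resources (k = 3) and adds USD 1,200 of prescriptions (k = 1). At resource cost the net is 1,200 − 1,000 = USD 200 extra. At charges it is 1,200 − 3,000 = −1,800, a USD 1,800 saving.

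**The case against.** The strongest reply is that the only ratio defined in section 12.2 has the program's direct costs in its numerator and no health care costs. A reader might infer that the planned cost per QALY is wrong, or that its numerator mixes program spending at cost with health care at charges. The text does not support that: health care costs stand in their own sentence. This part of the reply stands. What remains is that results are also to be reported as incremental cost-effectiveness from a societal perspective, and that future health care costs are to be discounted. Discounting them makes sense mainly if they enter the modeled result. That suggests netting, but the protocol does not say so.

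Second, section 12.2 commits to an expert panel's guidelines and to sensitivity analyses on any assumption, and a unit price is an assumption. This narrows the gap without closing it. Neither sentence names unit prices, and the base case stays on charges. The content of the guidelines is not in the protocol and is not relied on here.

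Third, the protocol does not define the prevailing community charge, and it could lie close to cost. Then k is near 1 and the bias is small. This is a fair limit on the size of the point.

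A reader might also infer that charges differing among the eight centers add noise. The protocol does not say whether charges are local or common, so that cannot be claimed.

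Finally, this is one input to the last of seven secondary aims. It leaves the primary analysis, error rates and power untouched.

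**Conclusion.** The point holds in a conditional form. Following the stated rule multiplies any between-arm cost-offset by the charge-to-cost ratio: 1.7- to 3.3-fold if cost is 30-60% of charge and the mark-up is the same for all services, both of which are assumptions. The same factor reaches any incremental or modeled cost per QALY that includes the offset. For a true offset of 20% of program cost, that ratio would be 17% to 58% too low; for extra care of the same size, 11% to 39% too high.

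The ratio of program direct cost to QALYs, as written, is unaffected. There is no bias if use does not differ between arms or if charges equal resource cost. Direction and size in this trial cannot be fixed from the protocol. The correction is worth making because the conflict with the societal perspective is explicit and cheap to remove.

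**What to change.** 1. In sections 6.2.14 and 10.6, replace the charge by one common schedule of unit costs in a single price year for all centers: national payment rates as a proxy for resource cost, or charges multiplied by a cost-to-charge ratio. Name the source. A payment rate is itself only an approximation to resource cost, and the text should say so.
2. Keep the charge-based result as a named sensitivity analysis.
3. In section 12.2, aim #7, state whether the health care cost difference enters the incremental ratio and the long-term model, or is reported only beside the direct-cost ratio.

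The questionnaire already records frequencies, so re-pricing needs no new participant data. The cost is a unit-price table and a few sentences. Some categories, such as telephone calls or prescriptions, may need a separate price source, and any reported saving may shrink.
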